## Abstract

**Background:**

Human mpox is a viral disease caused by an Orthopoxvirus, human mpox virus (hMPXV), typically causing fever and a rash. Mpox has historically been endemic to parts of Central and West Africa, with small numbers of imported cases reported elsewhere, but starting May 2022 an unprecedented global outbreak caused by clade IIb hMPXV was reported outside traditionally endemic countries. This prompted the initiation of MOSAIC, a cohort study implemented in Europe and Asia that aims to describe clinical and virologic outcomes of PCR-confirmed hMPXV disease, including those who receive antiviral therapy. The focus of this article, however, is on describing the study protocol itself with implementation process and operational challenges.

**Methods:**

MOSAIC recruits participants of any age with laboratory-confirmed mpox disease who provide informed consent. Participants enrol in the cohort for a total of six months. Blood, lesion and throat samples are collected at several timepoints from the day of diagnosis or the first day of treatment (Day 1) until Day 28 for PCR detection of hMPXV. Clinical data are collected by clinicians and participants (via a self-completion questionnaire) for six months to characterize the signs and symptoms associated with the illness, as well as short- and more long-term outcomes.

**Discussion:**

The design and prompt implementation of clinical research response is key in addressing emerging outbreaks. MOSAIC began enrolment within two months of the start of the international mpox epidemic. Enrolment has been stopped and the last follow-up visits are expected in January 2024.

**ICTRP registration:**

EU CT number: 2022-501132-42-00 (22/06/2022)

## Introduction

### Background and rationale

Mpox (formerly Monkeypox) is an acute viral disease caused by the human mpox virus (hMPXV), a member of the Orthopoxvirus family for which there are two distinct genetic clades, Clade I and Clade II
^
1,
2
^. Clade I is associated with higher morbidity and a case fatality rate of approximately 11%
^
3
^ and circulates primarily in parts of Central Africa. Clade II consists of two sub-clades–Clade IIa, historically detected in parts of West Africa (case fatality rate 0–4%
^
3
^), and Clade IIb, identified during the global outbreak starting in May 2022–sometimes also referred to as clade III
^
4
^.

The typical clinical features of human mpox closely resemble those of smallpox, although mpox is considered to be a milder disease. Clinical features of mpox are highly variable, but typically include distinctive centrifugal skin lesions, lymphadenopathy (which is not present in smallpox), fever, and other non-specific symptoms. However, in the 2022 clade IIb outbreaks, which mostly affected men who have sex with men
^
5
^, the clinical presentations differed from those described for cases in previous mpox outbreaks elsewhere. For example, 2022 clade IIb outbreak cases often presented with systemic symptoms typical for mpox, but with highly regional and sometimes more severe lesions, including oropharyngeal, genital, peroneal (peri-anal and ano-rectal lesions), frequently associated with other sexually transmitted diseases. Additionally, the incubation period was shorter (nine days compared to 13 days; range three to 34 days) for clade IIb outbreak cases, and the case fatality rate (CFR) was lower (
<0.01%) compared with the CFR previously reported for Clade II outbreaks in Africa [1.7–6.8%]
^
3
^.

The antiviral agent tecovirimat is the only mpox treatment licensed recently in Europe by the European Medicines Agency (EMA, in January 2022) and by the UK Medicine and Healthcare products Regulatory Agency (MHRA, in July 2022).
Approval was granted under ‘exceptional circumstances’, based on experimental and human safety data, but no clinical efficacy trial had been performed at that time. Tecovirimat, and the unrelated antiviral brincidofovir, are licenced for treatment of smallpox by
US Food and Drug Administration (FDA) under the ‘animal rule’.

The unprecedented 2022–23 international outbreak of clade IIb mpox is associated with over
91,000 cases reported in non-endemic countries from May 2022 and till present, of which around 26,000 confirmed cases have been reported in Europe and around 900 in Asia.

In response to the outbreak, the MOSAIC study was conceptualized on 20 May 2022, following a request from the EMA’s Emergency Task Force (ETF). MOSAIC was influenced by experience accrued through involvement in the ongoing tecovirimat expanded access programme (EAP) in the Central African Republic (CAR)
^
6
^, and selection of appropriate endpoints was aided by collaboration with researchers working on other studies, such as the
PALM-007 study in the Democratic Republic of the Congo. Here we describe the design of the ongoing MOSAIC study, progress to date, and some of the challenges experienced in executing the study.

This protocol has been written according to the SPIRIT guidelines
^
7
^.

## Methods

### Objectives

The primary objective of this study is to describe clinical outcomes of participants with laboratory confirmed MPXV, whatever the treatment administered.

Secondary objectives describe the virologic evolution of mpox, and Adverse Events (AEs) and Serious Adverse Events (SAEs) that occur in participants enrolled in the study. In France, additional exploratory objectives aim to evaluate virologic and immunological outcomes to learn more about viral transmission and induced immune responses. Among a subset of participants, exploratory objectives are to determine: i) the distribution of MPXV within the different anatomical sites of the participants, as well as the duration of positivity of the samples at the different sites, and the viral dynamics in patients receiving or not antiviral treatments (including tecovirimat), ii) the viability of the viruses detected by PCR (cell culture), iii) the intra-individual and inter-individual genetic variability, iv) the potential resumption of human immunodeficiency virus (HIV) viral replication in the blood and semen of participants living with HIV and the presence of other sexually transmitted infections, and v) post-mpox acquired humoral and cellular immunity.

### Trial design

MOSAIC is a multi-centre, multi-country cohort study enrolling participants with laboratory confirmed mpox for six months’ follow up. The study is an observational study in participating non-European Union (EU) countries, but has been classified as a Low Intervention Clinical Trial (LICT) in the EU–in accordance with the EU Clinical Trial Regulation (CTR) 536/2014
^
8
^, MOSAIC fulfils a LICT conditions as an authorised medicinal product, tecovirimat, is being used in compliance with its marketing authorisation (
*e.g.*, its use is not influenced by this protocol) and the study procedures do not pose more than minimal additional risk to the safety of its participants.

The study is designed with a tiered approach to protocol activities (
Figure 1 and
Table 1). Tier 1 activities–characterised by limited biological sampling and data collection–apply to all participants enrolled in the study. Tiers 2 and 3 apply only in France where participants are invited to give consent for additional, optional, activities associated with these tiers. Under these tiers, additional virologic (Tier 2) and immunological (Tier 3) investigations are carried out.

**Figure 1. f1:**
[figure not shown]
Tiered approach.

**Table 1. T1:** Schedule of procedures.

TIER				Baseline ^ a ^	Study days or Treatment days (D)																	
					D1	D2	D3	D4	D5	D6	D7	D8	D9	D10	D11	D12	D13	D14	D21	D28	D60	D180
**1**	**2**	**3**	*Windows permitted*															*±2 days*		*±2 days*	*±7 days*	*±7 days*
x	x	x	**Baseline assessment**																			
x	x	x	Consent	**X**																		
x	x	x	Demographics	**X**																		
x	x	x	Medical history ^ b ^	**X**																		
x	x	x	**Medical assessment**	**X**	**X**	*For patients who are hospitalised ^ c ^ or if a patient attends a pre-* *scheduled clinic visit*												**X**		**X**	X	X
x	x	x				X	X	X	X	X	X	X	X	X	X	X	X					
x	x	x	**Outcome assessment**															**X**		**X**	X	
x	x	x	**Sampling** ^ d ^																			
x	x	x	Two lesion swabs	**X**				X				X						**X**	X ^ e ^	**X**		
x	x	x	Throat swab	**X**				X				X						**X**	X ^ e ^	**X**		
	x	x	Mucosal lesion swab ^f,g^	X																		
	x	x	Saliva sample (using swab) ^f^	X								X						X		X	X ^h^	X ^i^
	x	x	Anus swab ^f^	X								X						X		X	X ^h^	X ^i^
x	x	x	Blood sample collection ^ e ^	**X**				X				X						**X**	X ^ e ^	**X**		
	x	x	Supplementary blood sample for serum	X				X				X						X		X	X	X
		x	Supplementary blood sample for plasma																	X	X	X
	x	x	Urine sample	X								X						X		X	X ^h^	X ^i^
	x	x	Semen or vagina secretions sample	X								X						X		X	X ^h^	X ^i^
x	x	x	**Participant self-assessment survey**	X	X	X	X	X	X	X	X	X	X	X	X	X	X	X	X	X	X	X
	x	x	**Participant social and sexual** **behaviour self-questionnaire**	X																		

*Note:* X in bold are data collection and sampling timepoint to prioritise.

^a^Baseline (could be anytime from D1) – baseline assessment and baseline medical assessment are done at enrolment; baseline samples are the participant’s diagnostic samples, which may have been collected for routine care before study participation commenced.

^b^Includes comorbidities, results of pregnancy and human immunodeficiency virus (HIV) tests, data on signs and symptoms experienced by the participant since their mpox diagnostic sample was collected, and details of potential adverse events (AEs) and serious adverse events (SAEs) occurring since their mpox diagnostic sample was collected.

^c^For hospitalised participants, hospital assessments should continue daily until the point of discharge

^d^Samples are only collected where feasible and permitted under local and national regulations on mpox infection prevention and control. Where local capacity limits sample collection, sites should prioritise the collection of D14 and D28 samples—all other samples are optional. Baseline samples are the participant’s diagnostic samples, which may have been collected for routine care before study participation commenced.

^e^An additional sample should be collected at D21 if the participant has a positive PCR on D14.

### Outcomes

**
*Primary outcome measure.*
** The primary outcome measure of this study is the participant’s time to lesion resolution without any serious complications. Lesion resolution is the first day on which all lesions are resorbed, scabbed or desquamated and mucosal ulcers healed. Lesion resolution is assessed until a maximum of 14 days since the date that the diagnostic sample is taken (for participants who do not receive mpox-specific antiviral treatment) or the day of treatment initiation (for participants who receive mpox-specific antiviral treatment).

**
*Secondary outcomes.*
** Secondary outcome measures evaluate clinical and virologic outcomes. Clinical outcomes are assessed on the basis of:

1. Clinical status on day 14 and day 28 according to a four-point ordinal scale assessed by a physician or a study nurse. The ordinal scale is a) all lesions are resolved and no serious complications, b) active lesions and no serious complications, c) serious complication and/or hospitalization due to mpox, or d) death.2. Evidence of recrudescence or relapse at day 60 and day 180.

*Note:* A "serious complication" is any complication associated with a Serious Advent Event (SAE) that is life-threatening, results in hospitalisation, prolongation of existing hospitalisation, disability, incapacity, or a congenital anomaly; or any other complication that is considered medically significant.

Virologic outcomes in Tier 1 are assessed on the basis of:

1. Change from baseline in mpox virus DNA levels in throat swabs on days 4, 8, 14 and 28.2. Change from baseline in mpox virus DNA levels in blood on days 4, 8, 14 and 28.3. Presence of mpox virus DNA in lesion swabs on days 4, 8, 14 and 28.

The study also assesses the number and type of SAEs, Suspected Adverse Reactions (SARS) and Suspected Unexpected Serious Adverse Reactions (SUSARs) within 28 days of enrolment.

Pregnancy outcomes defined as the final known health status of the mother and child are evaluated in any participants who are pregnant during the course of the study.

**
*Exploratory outcomes in Tier 2 and Tier 3.*
** Further virologic and immunological outcomes are also evaluated in France under this protocol to learn more about viral transmission, humoral and cellular immune responses. The outcome measures are as follows:

Detection and quantification of MPXV using different PCR tools from different body samples (skin lesions, mucosal lesions, blood, urine, genital secretions, oropharynx, saliva, anus) at baseline, D8, D14 and D28. Additional samples are collected and tested at D60 and D180 if participants receive a positive result at D28 or D60, respectively;Capacity of MPXV to infect cells, and replicate, investigated by cell culture and MPXV detection from supernatant at baseline;Genetic diversity of MPXV between the participants and between the different anatomical sites, assessed with MPXV deep sequencing;Detection of syphilis using serological test, and other sexually transmitted infections (STIs) (
*Chlamydia trachomatis*,
*Neisseria gonorrhoeae*,
*Mycoplasma genitalium*) using PCR from urine, anus and oropharynx, at baseline;Quantification of HIV viral load from blood and semen in participants living with HIV at baseline, D8, D14 and D28;Description of social and sexual behaviours in the months prior to inclusion;Quantification of plasma antiviral concentrations;Assessment of the diversity of genetic immune host factors;Quantification and dynamic of the humoral and neutralizing memory B cell responses, as well as the cellular T cell response, over time, at baseline, D14, D28, D60 and D180.

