### Participant timelime

Enrolment is the day that the informed consent form is signed, and the participant is enrolled in the study. Enrolment may be any day once the diagnostic sample is taken or after the patient has been considered a “presumptive case” by their treating clinician.

After enrolment, days are counted from the date the diagnostic sample is taken:

Day 1 is the date that the first sample to diagnose mpox was taken, regardless of when results became available. If the participant is enrolled on the same day that the diagnostic sample is taken, enrolment occurs on Day 1.If a participant is enrolled after the date that the diagnostic sample was taken, then study procedures start from the number of days since the sample was taken.

Participants who do not receive treatment follow the schedule from D1 and continue until D180. Participants who receive treatment immediately following diagnosis and enrolment in the study follow the schedule described above.

If a participant enters the study without receiving treatment and then begins receiving treatment at a later date, they initiate a new schedule of procedures by restarting at D1. This second D1 represents the date of treatment start. This extends the study participation period by the number of days between enrolment and treatment initiation.

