### Statistical method

**
*Sample size.*
** This is an observational study. We are interested in the effect of any available treatment against mpox used in the cohort and thus defined treatment outcomes (see below). However, due to the observational nature of this study, there is no formal sample size calculation to assess treatment effect. The availability of treatments and prescription rules differ in time and across countries. Any causal inference analysis will account for confounding effects, pre-specified in the statistical analytical plan.

**
*Participant flowchart.*
** The total number of patients and the flowchart of the study will be presented with the number of patients excluded (with reasons for exclusion, and number of patients for each reason), included, receiving any antiviral drugs, lost-to-follow-up and analysed.

**
*Descriptive statistics.*
** Patients’ demographics and baseline characteristics will be described overall and across analysis groups (
*e.g.*, treated with and without tecovirimat), by using, for continuous variables: sample size, mean, standard deviation, median, interquartile range, minimum and maximum; and for categorical variables: sample size, proportion and number of patients in different categories.

The number of missing values, overall and per group, will be reported.

**
*Inferential statistics.*
** Causal inference methods will be used to derive information on the effects of tecovirimat (or other antiviral drugs) on patients’ outcomes (see below) and assessed from a Cox proportional hazard model. Graphics and tables associated to the analysis of each outcome will be fully detailed in the SAP.

**
*Primary outcome.*
** The time to lesion resolution will be summarized for the overall population and stratified by treatment status using Kaplan-Meier curves, median time-to-event, proportion of resolution at D14, and associated 95% confidence intervals (CIs).

**
*Secondary outcomes.*
** For clinical status at D14 and D28, counts and percentages will be presented with their associated 95% CI. The four-point ordinal scale will be used to estimate a proportional odds model. Recrudescence or relapse will be compared between treatment status with a logistic regression model.

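### The primary outcome is timed from the diagnostic sample in untreated participants but from treatment start in treated ones, so its summaries by treatment status compare different illness days

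*Protocol article*

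**What the plan says.** Outcomes (Primary outcome measure): "Lesion resolution is assessed until a maximum of 14 days since the date that the diagnostic sample is taken", and the sentence goes on "for participants who do not receive mpox-specific antiviral treatment) or the day of treatment initiation (for participants who receive mpox-specific antiviral treatment". The Methods paragraph of the Abstract gives Day 1 the same two meanings.

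Participant timeline: the general rule is "Day 1 is the date that the first sample to diagnose mpox was taken, regardless of when results became available". For participants who enter untreated and start treatment later, "they initiate a new schedule of procedures by restarting at D1. This second D1 represents the date of treatment start". A third sentence reads: "Participants who receive treatment immediately following diagnosis and enrolment in the study follow the schedule described above".

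Statistical method (Primary outcome): time to lesion resolution "will be summarized for the overall population and stratified by treatment status using Kaplan-Meier curves", with medians, the proportion resolved at day 14 and 95% confidence intervals. Under Inferential statistics, the effects of tecovirimat or other antivirals are to be derived with causal inference methods and "assessed from a Cox proportional hazard model". Confounders are left to the SAP; the examples given under Adjusted analyses are age, smallpox vaccination and extent of lesions.

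**The concern.** The start of the clock depends on the exposure being compared. Someone treated d days after the sample has the first d unresolved days dropped and is judged at day 14 + d after the sample. An untreated participant is judged at day 14. Someone who heals before treatment could begin is untreated by definition. Adjusting for characteristics at baseline does not line up two different baselines.

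What is at stake is the reading of the treated and untreated curves, medians and day-14 proportions on the primary outcome, and possibly the treatment hazard ratio. Part of any difference could come from the clocks and not from the drug.

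Delays are to be expected. The protocol has a rule for treatment begun later, it dates Day 1 from the sample even when the result comes later, and its Discussion says that tecovirimat was scarce when cases were peaking.

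**Working it through.** **Inputs from the protocol.** The two origins and the 14-day limit (Outcomes); 601 enrolled, with 55 + 7 + 2 = 64 treated if the three counts do not overlap, so 64/601 = 10.6% (Discussion). The protocol states no sample size, power or effect size, so there is no figure to reproduce.

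**Assumed, because not given.** Time from sample to healing is Weibull with median m of 10 or 14 days and shape k from 1 (constant hazard) to 3 (steeply rising). The delay to treatment is varied. Treatment has no effect, and there is no confounding.

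**Step 1: day-14 proportions by formula.** With S(t) = exp(−ln 2 · (t/m)^k), a participant still unresolved at day d and treated then is resolved by day 14 of the treatment clock with probability P(d) = 1 − S(d + 14)/S(d).

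For m = 14, k = 2, d = 3: S(17) = exp(−0.693 × 1.474) = 0.360 and S(3) = exp(−0.693 × 0.0459) = 0.969, so P = 1 − 0.360/0.969 = 63%. At d = 0 it is 50%.

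| Shape k (m = 14) | d = 0 | d = 1 | d = 3 | d = 5 |
|---|---|---|---|---|
| 1 | 50% | 50% | 50% | 50% |
| 1.5 | 50% | 53% | 58% | 61% |
| 2 | 50% | 55% | 63% | 70% |
| 3 | 50% | 57% | 71% | 82% |

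All of the gain over 50% comes from the later clock.

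**Step 2: Cox model on the protocol's clocks.** Simulated cohorts (400,000 per scenario, 11% planned for treatment, treatment given only if still unresolved, Poisson delay, follow-up cut at 14 days on each clock). A hazard ratio above 1 means faster resolution in the treated; the range is over m = 10 and 14.

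| Shape k | Delay 0 | Mean 1 day | Mean 3 days | Mean 5 days |
|---|---|---|---|---|
| 1 | 1.00–1.01 | 0.98 | 0.96 | 0.95–0.96 |
| 1.5 | 1.00 | 1.09 | 1.23–1.25 | 1.35–1.36 |
| 2 | 1.00 | 1.15–1.16 | 1.45–1.50 | 1.74–1.83 |
| 3 | 0.99–1.01 | 1.24–1.28 | 1.85–1.94 | 2.56–2.88 |

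At k = 2, m = 14 and a mean delay of 3 days, 62% of treated and 50% of untreated participants are resolved by day 14, in line with step 1.

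**Step 3: sensitivity to the assumptions.** A right-skewed delay averaging about 2.4 to 2.7 days in the treated gives 1.35–1.36 at k = 2 and 1.61–1.67 at k = 3. With an average of about 1.4 days, k = 2 gives 1.21. Differences between patients flatten the population hazard. At k = 2, m = 14 and a mean delay of about 2.5 days, gamma frailty with variance 1 lowers the hazard ratio to about 1.2 (1.17–1.25 across runs), and variance 2 to about 1.1 (1.08–1.13).

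**Step 4: two candidate repairs under the same null.** One clock from the sample with treatment as a time-dependent covariate gives 0.99 to 1.01 in every scenario of step 2. One clock from the sample with participants classed as ever-treated from day 1 gives 0.44 to 1.01 over mean delays of 0 to 7 days. That is immortal time bias in the other direction.

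**The case against.** **The Cox analysis may be sound.** The protocol promises causal inference methods and defers details to a SAP that is not shown. That SAP could use time-dependent treatment or a target-trial emulation. This stands: a reader might infer that the Cox comparison is biased by design, but the text shows only that it will be if the outcome is used as defined. The objection does not reach the Kaplan-Meier curves, medians and day-14 proportions by treatment status, which the protocol itself fixes. Nor does the stated promise, which covers confounding, mention time zero.

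**The direction is not known.** A reader might infer that an inert drug will look effective because lesions heal with time. Healing over time is also compatible with a constant or falling hazard. The protocol gives neither a healing distribution nor a delay, and it describes the clinical features as highly variable. This stands, so the size is conditional.

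**The Outcomes section literally sets when assessment ends, not when the clock starts.** True. That the same dates are Day 1 comes from the Abstract and the Participant timeline section. Even on the literal reading, the horizon differs by treatment.

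**The study is primarily descriptive.** The overall summary does not depend on the treatment comparison, but the Statistical method section also states an aim of estimating treatment effects.

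**The conflict over Day 1 is small.** A reader might see a contradiction for participants already on treatment at enrolment. The Participant timeline section governs the schedule of procedures and has no sentence on that group. For those treated immediately, the two dates may be close. Only a need for clarification remains.

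**Conclusion.** The concern holds for what the protocol fixes: the primary outcome has two origins set by treatment, and it is summarised by treatment status. It extends to the Cox model only if the SAP takes the outcome as written.

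Under a true null, the distortion is nil at zero delay and slightly against treatment with a constant hazard (0.95 to 0.98). With Weibull shape 2 it is about 1.15 to 1.2 for mean delays of 1 to 1.5 days and 1.35 to 1.5 for 2.5 to 3 days, falling to about 1.2 with moderate heterogeneity between patients. With shape 3 and 2.5 to 3 days it is about 1.6 to 1.7 for a skewed delay and up to 1.9 for a Poisson one. These figures rest on assumed healing and delay distributions without confounding. They show what the clocks alone can do and do not estimate the bias in this cohort.

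**What to change.** For every comparison of treated with untreated participants, use one origin, the diagnostic sample date, and one horizon in days since that date. In the Cox model, count participants as untreated until treatment starts and as treated afterwards; a sequential or clone-censor-weight target-trial emulation would also serve. Do not move everyone to the sample date and class them as ever-treated from day 1.

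Replace the Kaplan-Meier curves, medians and day-14 proportions by ever-treated status with landmark or weighted versions. Keep time since treatment start as a description within the treated group only.

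As a minor clarification, reconcile the Outcomes and Participant timeline sections on which date is Day 1 for participants treated immediately.

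The cost is analysis wording and modest programming; the sample and treatment dates are already needed for the plan's own clocks. The downsides are a slightly more complex model, less post-treatment follow-up inside a common 14-day horizon for those treated late, and possibly less favourable treated results. Confounding by indication is a separate problem that still needs its own adjustment.
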